## Abstract

**Background:**

Chronic kidney disease (CKD) and end-stage kidney disease (ESKD) are serious and growing health problems with enormous impact on psychological and social functioning. Despite high rates of comorbid depression and anxiety in these patient populations, and the adverse impact these have upon treatment adherence, quality of life, social connectedness and healthcare costs there has been little attention focused on the prevention or management of these problems. Thus, our aim was to evaluate the Dialysis Optimal Health Program (DOHP) that adopts a person-centred approach and engages collaborative therapy to educate and support those diagnosed with ESKD who are commencing dialysis.

**Methods:**

The study design is a randomised controlled trial. Ninety-six adult patients initiating haemodialysis or peritoneal dialysis will be randomly allocated to either the intervention (DOHP) or usual care group. Participants receiving the intervention will receive nine (8 + 1 booster session) sequential sessions based on a structured information/workbook, psychosocial and educational supports and skills building. The primary outcome measures are depression and anxiety (assessed by the Hospital Anxiety and Depression Scale; HADS). Secondary outcomes include health-related quality of life (assessed by the Kidney Disease Quality of Life instrument; KDQOL), self-efficacy (assessed by General Self-Efficacy Scale) and clinical indices (e.g. albumin and haemoglobin levels). Cost-effectiveness analysis and process evaluation will also be performed to assess the economic value and efficacy of the DOHP. Primary and secondary measures will be collected at baseline and at 3-, 6-, and 12-month follow-up time points.

**Discussion:**

We believe that this innovative trial will enhance knowledge of interventions aimed at supporting patients in the process of starting dialysis, and will broaden the focus from physical symptoms to include psychosocial factors such as depression, anxiety, self-efficacy, wellbeing and community support. The outcomes associated with this study are significant in terms of enhancing an at-risk population’s psychosocial health and reducing treatment-related costs and associated pressures on the healthcare system.

**Trial registration:**

ANZCTR no. 12615000810516. Registered on 5 August 2015.

**Electronic supplementary material:**

The online version of this article (doi:10.1186/s13063-016-1558-z) contains supplementary material, which is available to authorized users.

## Background

Escalating prevalence and incidence rates of chronic kidney disease (CKD) and end-stage kidney disease (EKSD) are a global challenge [1]. In 2012, around 10 % of Australians (1.7 million) aged 18 and over exhibited measured biomedical signs of CKD; of these, 97 % showed early signs of CKD (stages 1–3) [2]. The overall prevalence of Australians aged 25 and over with ESKD has increased by approximately 20 % from 2005 to 2010 [3]. Dialysis is a challenging experience for most patients, especially in the first year [4–6], with high economic and personal costs to patients and their families, and considerable economic and planning implications for the healthcare system [7]. Commonly reported symptoms of CKD and ESKD include: loss of appetite; insomnia; high blood pressure; and swelling of feet and ankles. Consequently, the disease burden on quality of life is significant [1]. Thus, the patient and family find themselves dealing with multiple disease-associated stressors including balancing the restrictions of this disease within the context of their intimate relationships, families, social networks, treatments, and cultures. Psychological distress, as in other chronic physical diseases, is common in individuals with CKD and ESKD with rates considerably above those in the general population [8–12]. The randomised controlled trial (RCT) described here will adopt a person-centred approach combining collaborative therapy and care coordination to support and improve the psychosocial health and quality of life of those living with CKD and ESKD.

### CKD/ESKD psychosocial interventions

In addition to the increased risk of hospitalisation in ESKD patients with comorbid mental health issues [13], several studies have reported the effect of depression on chronic haemodialysis patient survival to be of similar magnitude to that of medical risk factors [14, 15]. The mechanisms linking depression with survival in this population are unclear but may be related to factors such as treatment adherence, nutritional issues, perceptions of illness, personality, coping styles and increased perception of social support. Adverse biological consequences of the depressed state, including inflammatory, autonomic and neuroendocrine effects also play a role [10]. Psychological distress may also influence a patient’s decision to withdraw from dialysis, accepting palliation, with a recent study finding depression to be significant factor in this decision, particularly where symptoms are apparent in the early stages after commencement of dialysis [14].

A recent review of self-management programs in CKD identified weak evidence that their delivery alone can improve adherence [16]. The authors of that review concluded that life contexts, socioeconomic factors, health literacy and psychological factors, as well as communication with healthcare providers, all contribute to an individual’s adherence to treatment. For example increased psychological distress and poorer communication with healthcare providers was associated with reduced treatment adherence. This review further identified that self-efficacy skill building could potentially improve adherence and therefore be a target for psychosocial interventions [16]. In addition, social processes such as social support can influence psychological changes at an individual level, which may then lead to modified health behaviours. Psychosocial factors are important because they enhance quality of life, in turn slowing the progression of various chronic diseases [17].

The burden and role of depression, anxiety, quality of life and social support in adults with CKD prior to renal replacement therapy was examined in a recent review of the literature [18]. Although the evidence for the impact of psychosocial factors was sparse, the authors did identify that depression and depressive symptoms may independently predict progression to dialysis, hospitalisation and death [18]. However, investigations into the impact of anxiety disorders, social support and quality of life on the clinical course of CKD have received minimal attention. The authors recommended large-scale prospective cohort studies to clarify the burden and prognostic impact of psychosocial factors in this vulnerable population [18].

Although psychosocial interventions are effective in the treatment of anxiety and depression, they have not yet been deployed or evaluated in the ESKD population. To date, there have been no published randomised controlled trials assessing the efficacy of psychosocial interventions for improving depression in ESKD, albeit there is some clinical evidence that these interventions might be effective [19, 20].

### Translating Research, Integrated Public Health Outcomes and Delivery (TRIPOD)

This RCT is part of a larger research program – TRIPOD – which will evaluate our Optimal Health Program (OHP) across three chronic conditions; namely CKD/ESKD, diabetes mellitus and stroke, inclusive of cost-effectiveness analyses. Based on a collaborative therapy framework (CTF; consists of three core components - *education* relating to factors that influence mental health, *coping strategies* that help manage stress and adjustment to illness, and *skills development* to manage stress, illness and long-term optimal health) the OHP was originally developed to support people with mental illness [21]. The initial trial, in an adult mental health service, demonstrated significant improvements in health and social functioning, a reduction in hospital admissions and net cost savings per patient [22]. A key aspect of collaborative therapy is recognising that ‘recovery’ and chronic models of health care are not dichotomous [23]. With the intention of enhancing self-efficacy, self-management, care co-ordination and quality of life, the OHP has been adapted within the broader context of chronic disease. Thus, in the current series of trials our OHP is used to implement this therapeutic framework to enable clinicians and consumers to work systematically towards the achievement of optimal psychosocial health outcomes within mainstream health services. The self-management foundations of the OHP are particularly relevant for adults with ESKD who face the daily challenge of managing various and often simultaneous aspects of their disease such as managing multiple medications, fluid and food intake, ongoing appointments, and monitoring of blood pressure as well as coping with the emotional impact of their care regimen. This protocol describes an RCT to evaluate a dialysis optimal health program (DOHP), a program specifically designed for people living with stage 5 CKD/ESKD.

### DOHP pilot studies

Adaptation of the OHP for people with ESKD was informed by clinical evidence, a review of the associated literature, and pilot data. Two studies, both conducted at St Vincent’s Hospital (Melbourne) were initially conducted that provided (1) information to assist with the development of DOHP and (2) evidence as to the feasibility of DOHP. The first study was a cross-sectional survey of 27 adult patients receiving either haemodialysis or peritoneal dialysis. The aim of this study was to explore the impact of ESKD on individual illness perceptions, coping styles and psychological wellbeing. Key findings indicated that perceptions of illness rather than actual symptoms best accounted for patients’ adaptation to ESKD. Given that the focus of the OHP is to support the patient’s psychological wellbeing, using strategies to improve self-efficacy, empower patients and enhance their self-management skills, these initial findings provided evidence for the suitability of an adaptation of the OHP to those experiencing ESKD and initiating dialysis.

Pilot data was also collated via a RCT (*n* = 12) of the DOHP versus standard care. Patients from a metropolitan and a rural dialysis service were followed over a 12-month period from initiation of dialysis. There were two deaths and one further withdrawal, leaving nine patients who completed the study. Primary outcomes were depression and anxiety. Secondary outcomes included quality of life, treatment adherence, perceived social support, level of function, episodes of psychiatric illness and treatment, medical morbidity and health care utilisation (e.g. outpatient visits; hospitalisations) [10]. An analysis of incidence of depression and anxiety, based on regular face-to-face and phone call assessments using the Mini-International Neuropsychiatric Interview (MINI 6.0) [24], identified incidents of depression and anxiety in the control group only (depression × 3; anxiety × 4). Due to the small size of the trials, conclusions regarding the potential benefit of OHP in relation to the primary and secondary outcomes were not able to be made. However, in relation to the feasibility of the trial, it was clear from participant feedback that the OHP program was associated with high satisfaction, perceived development of skills to effectively manage problems, and would be recommended by others [10].

### Research aims

The aim of this research is to determine whether a dialysis-specific OHP (DOHP) will improve the psychosocial health of dialysis patients, compared to usual care. The primary objective is to identify the impact of DOHP on levels of depression and anxiety in those receiving dialysis. Secondary objectives are to evaluate the impact of DOHP on quality of life, self-efficacy, social and workplace functioning, self-management, and illness perceptions of and coping with ESKD.

A full economic evaluation, namely, cost-effectiveness analysis will be performed to provide further evidence on the efficiency of the DOHP by outweighing health gain and impact on the use of health resources associated with DOHP. The perspectives are from the Australian healthcare system and the patient/family. Quality-adjusted life years (QALYs) will be measured using the Assessment of Quality of Life-6D (AQoL-6D) [25] and European Quality of Life-5 dimensions (EQ-5D-3L) [26]. Process evaluation including focus group interviews will also be conducted with patient and staff participants to assess the effectiveness of the DOHP, implementation, and uptake and service delivery.

## Methods

### General design

This is a prospective randomised controlled trial to evaluate the effectiveness and cost-effectiveness of the OHP specifically adapted for patients receiving dialysis. The DOHP will be delivered as a 9- (8 + 1) week individualised support program using health promotion strategies and will be compared to usual care. Assessments will take place at baseline, 3, 6, and 12 months post-baseline. The study protocol was approved by the St Vincent’s Hospital Human Research Ethics Committee (HREC-A 019/14). An executive steering committee consisting of a nephrologist, a specialist renal nurse, psychologists, psychiatrists, nurses and a health economist oversees project planning, procedures and ongoing data collation.

### Setting

The study will be conducted at the nephrology unit of St Vincent’s Hospital, a large metropolitan teaching hospital in Melbourne, Australia. As of March 2015, the dialysis unit had 290 patients with ESKD receiving dialysis and 190 referred for medical management of CKD with treatment aim of preserving kidney function. The necessary volume of clinical cases and expertise required for this study was established within St Vincent’s nephrology unit in the piloting phase of this research.

### Participants

A minimum of 96 patients initiating dialysis will be recruited into the study. The type of dialysis is haemodialysis, peritoneal dialysis or home dialysis, or collectively known as ‘dialysis’. The following criteria must be met for inclusion in the study: (1) diagnosis of near ESKD confirmed by medical records; (2) expected to commence maintenance dialysis for the first time in the next 3 months or commencement of dialysis in the past 3 months; (3) aged 18 or above; and (4) able to converse in English without an interpreter. Exclusion criteria are: (1) presence of developmental disability or amnestic syndrome impairing their ability to learn from the intervention; (2) participants returning to dialysis following a failed renal transplant; and (3) comorbid serious illness as defined by the treating physician. Individuals who are seeking a mental health professional or taking psychotropic medications will not be excluded from participating.

Power was calculated to detect a medium effect size of *d* = 0.40 using a sample size formula comparing time-averaged differences for continuous outcomes in repeated measurement studies [27]. The power calculations assumed the following: (a) two primary outcome measures (HADS anxiety and depression severity scores); (b) four assessment points (i.e. baseline, 3, 6, and 12 months); (c) a between-repeated measures ρ = 0.70; (d) a study-wide type I error of 0.05 (i.e. a single test α of 0.05 ÷ 5 or 0.01); (f) a type II error rate (β) of 0.20 (power of 0.80); and (g) two-tailed statistical tests. The within-subject correlation (0.70) was based upon a previous OHP trial that demonstrated high correlations over time [22]. The power analysis indicated that 38 participants would be required in each group. Allowing for an attrition rate of 20 %, a total of 96 participants, or 48 in each arm, will be recruited.

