#### Randomisation and blinding

Following the initial screening and gaining of consent, participants will be allocated to either intervention or control group via a computer-generated block randomisation sequence created by an independent person not directly involved in the study. Due to the nature and length of the intervention, it is not possible to blind either patient or investigator to the intervention allocation.

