Due to variability of usual care in the control group, key aspects of standard care will be assessed via responses to the HCUQ [39]. Medical records will also be accessed to confirm diagnostic information, inpatient, outpatient and emergency department visits.

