### Statistical analyses

Intention-to-treat analysis will be employed to prevent overestimation of intervention efficacy. Categorical variables will be analysed using chi-squared tests (or Fisher’s exact test for small samples). A mixed-effects model, repeated measures (MMRM) approach will be used to examine the longitudinal profile of the two primary outcome measures at the three time points (3, 6 and 12 months post-baseline). For all MMRM analyses, baseline scores will be used as covariates and the models will include prespecified fixed effects of treatment, clinician and time, in addition to treatment-by-time and treatment-by-clinician interactions. Appropriate adjustments for multiple primary (depression and anxiety) tests will be made, i.e. Bonferroni correction to ensure the risk of type I error is maintained at 5 %. The potential impact of any additional care received by some participants will be assessed in a separate regression analysis using analysis of covariance.

Secondary analyses using analysis of covariance will be conducted to compare change scores during treatment and follow-up points for primary, secondary and process outcomes using the fixed, continuous covariate of baseline score as well as the categorical fixed effects of treatment group, clinician and treatment-by-clinician interactions. Following this, all secondary outcome measures will be assessed, as per above using first a MMRM and then assessing change scores.

Although the attrition rate is not expected to vary by group (intervention vs usual care), we will attempt to identify key predictors of attrition status (i.e. demographic or clinical baseline characteristics) and test for differences between groups. Assuming the data are missing at random, several procedures offer effective approaches that may attenuate attrition. For example, multiple imputation procedures that utilise the expectation-maximization (EM) algorithm with bootstrap estimates of standard errors will be used. A maximum likelihood model with time as a random variable will allow the use of all available data from all assessments, reducing bias and increasing power [40]. Application of these procedures has been shown to provide unbiased estimates, even in the face of substantial missing data [41].

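### The primary HADS models do not adjust for psychotropic use or mental health care at entry, although such patients are admitted: a modest loss of precision, not a bias

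*Protocol article*

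**What the plan says.** All references are to the protocol article.

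- **Participants:** "Individuals who are seeking a mental health professional or taking psychotropic medications will not be excluded from participating".
- **Randomisation and blinding:** patients are "allocated to either intervention or control group via a computer-generated block randomisation sequence". No stratification factor is named.
- **Statistical analyses, primary model:** "For all MMRM analyses, baseline scores will be used as covariates". The other terms are "prespecified fixed effects of treatment, clinician and time, in addition to treatment-by-time and treatment-by-clinician interactions". No term represents psychiatric treatment at entry.
- **Statistical analyses, concurrent care:** "The potential impact of any additional care received by some participants will be assessed in a separate regression analysis using analysis of covariance". Additional care is not defined, and neither is the period it covers.
- **Outcome measurements:** "Due to variability of usual care in the control group, key aspects of standard care will be assessed via responses to the HCUQ". Table 1 schedules the HCUQ at baseline and at every follow-up.
- **Intervention: DOHP:** facilitators discuss and arrange referrals to other services, so care after allocation can be a consequence of the intervention.

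**The concern.** Psychotropic medication and mental health care are aimed at the two primary outcomes, depression and anxiety. Baseline HADS captures much of their influence but perhaps not all. Two patients with the same score may have different expected courses if one is under treatment and the other is not.

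The article fixes a covariate set and leaves this status out. The one analysis that touches concurrent care may condition on care received after randomisation, some of it arranged by DOHP facilitators. Adjusting for that could remove part of the effect under study, so it does not replace a covariate fixed before allocation.

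Two things are at stake: some precision in a small trial, and the reading of the result if the arms turn out to differ. A covariate first added once an imbalance has been seen, in a trial that cannot blind patient or investigator, is open to challenge as data-driven.

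**Working it through.** **Inputs from the article (Participants).** Target d = 0.40; within-subject correlation 0.70; 38 per group before attrition; 20% attrition. The attrition step reproduces: 38 / 0.8 = 47.5, rounded up to 48 per arm. The article gives no figure on psychiatric treatment at entry.

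**Assumed inputs.** Prevalence p of treatment at entry, 10–40%. Residual effect g on follow-up HADS after adjustment for baseline, 0.1–0.5 SD, with 0.3–0.5 SD as the case where adjustment is worth having. Two-sided alpha of 0.025 per outcome, which is Bonferroni for two primary outcomes.

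**1. How large can a chance imbalance be?** The SD of the between-arm difference in proportions is sqrt(2p(1−p)/n).

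| n per arm | p | SD | P(difference of 10 points or more, either way) |
|---|---|---|---|
| 48 | 15% | 0.073 | 0.17 |
| 48 | 20% | 0.082 | 0.22 |
| 48 | 30% | 0.094 | 0.29 |
| 38 | 15% | 0.082 | 0.22 |
| 38 | 20% | 0.092 | 0.28 |
| 38 | 30% | 0.105 | 0.34 |

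**2. What does an imbalance do to the estimate?** Shift = g × imbalance. For 10 points: 0.3 × 0.10 = 0.03 SD and 0.5 × 0.10 = 0.05 SD. With 48 per arm, the 95% limit of the shift (1.96 × SD × g) runs from 0.012 SD (p = 10%, g = 0.1) to 0.098 SD (p = 40%, g = 0.5). It is 0.055 SD at p = 30%, g = 0.3.

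**3. Is the test invalid without the term?** ANCOVA on the mean of three follow-ups was simulated with 48 per arm and 10,000 runs per scenario. The residual variance was (1 + 2 × 0.70)/3 − 0.70² = 0.80 − 0.49 = 0.31. Clinician terms and dropout were not modelled.

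| p | g | Type I error without / with term | Power at d = 0.40 without / with term |
|---|---|---|---|
| 20% | 0.3 | 0.0251 / 0.0248 | 0.867 / 0.878 |
| 30% | 0.3 | 0.0224 / 0.0229 | 0.860 / 0.879 |
| 30% | 0.5 | 0.0245 / 0.0229 | 0.830 / 0.882 |

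The mean estimate was unbiased either way. The gain in power is 1.0, 2.0 and 5.2 points.

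**4. The wider prevalence range.** Without the term the residual variance is about 0.31 + g²p(1−p), and power is about Φ(0.40 / sqrt(2 × variance / 48) − 2.241).

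- With the term: variance 0.31, power 0.899.
- p = 10%, g = 0.3: variance 0.318, power 0.891, gain 0.8 points.
- p = 40%, g = 0.5: variance 0.370, power 0.837, gain about 6 points.

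**5. Given a 10-point imbalance.** The shift is 0.03/0.117 = 0.26 to 0.05/0.122 = 0.41 standard errors. For an imbalance that works against the control arm or against DOHP alike, the two-sided rejection rate under no effect is then roughly 0.030 to 0.038 instead of 0.025.

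**The case against.** A reader might infer that chance imbalance in psychiatric treatment will be read as a DOHP effect. The documents do not support that. Under randomisation, chance imbalance in any prognostic factor is already covered by the standard error and alpha, and step 3 shows this. The shift in step 5 is conditional on an imbalance having occurred, and across randomisations it averages out.

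Further objections, and what stands of each:

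- **Both driving inputs are assumed.** This stands. If the residual effect is near 0.1 SD, the gain is negligible.
- **A yes/no term codes new and long-standing treatment alike.** This stands. The term captures only the average difference between treated and untreated patients, which may be smaller than 0.3–0.5 SD.
- **The data may not exist.** This stands in part. Outcome measurements says the HCUQ covers outpatient and community care, so mental health visits are plausibly recorded. The PBS is named only as a price source, and the records are accessed for diagnoses and visits. Nothing says that psychotropic use is captured at baseline.
- **Concurrent care was considered.** This is true of the HCUQ and the separate ANCOVA, but an undefined and possibly post-allocation measure is no substitute for a baseline covariate.
- **Stratification may be described in the full protocol.** This is fair. The lack of a named stratification factor is not held against the plan.
- **The same argument could be made for other prognostic factors.** True. What sets this one apart is that it acts on both primary outcomes and that the eligibility text expressly admits it.

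**Conclusion.** The point holds as a modest gain in precision and clarity. Admitting these patients is a legitimate choice, and the planned analysis is valid without the extra term.

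What is forgone is about 1 to 5 points of power at 20–30% prevalence with a residual effect of 0.3–0.5 SD, and about 1 to 6 points across 10–40%. A realised 10-point imbalance, with a probability of 17–29% at 15–30% prevalence and 48 per arm, would leave an unadjusted shift of 0.03–0.05 SD, roughly a tenth of the target effect. All of these figures rest on a prevalence and a residual effect that the documents do not give.

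The weaker part of the current text is the ANCOVA on additional care. Without a definition and a time frame, it may adjust for something that DOHP itself changes, and its result could not be read as a correction to the primary estimate.

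**What to change.** In Statistical analyses:

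1. Add one prespecified fixed effect to both primary HADS models: psychotropic medication or contact with a mental health professional before randomisation (yes/no). Take it from the baseline HCUQ and the medical record, after confirming that psychotropic use is recorded there.
2. Report its distribution by arm in the baseline table.
3. State that this baseline status is distinct from care received after allocation. Define additional care and its period, and label that ANCOVA exploratory.

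If the sponsor prefers to keep the primary model as it is, the adjusted model can be prespecified as a sensitivity analysis. That protects the reading of an imbalance but not the precision of the primary test.

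Cost: a few lines of text, one degree of freedom, and possibly one extra baseline item. If recruitment is too far advanced for a new item, the indicator depends on what the HCUQ and the records already hold. Because the term is fixed before allocation, it introduces no bias.

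### The power calculation sets a per-test level of 0.05/5 = 0.01, but Bonferroni over the two named primary tests implies 0.025

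*Protocol article*

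**What the plan says.** Three statements in the protocol article bear on this.

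- **Number of primary tests, planning.** The power assumptions in Participants list "two primary outcome measures (HADS anxiety and depression severity scores").
- **Per-test level, planning.** The same list gives "a study-wide type I error of 0.05 (i.e. a single test α of 0.05 ÷ 5 or 0.01"), with "two-tailed statistical tests" and "a type II error rate (β) of 0.20 (power of 0.80").
- **Multiplicity rule, analysis.** Statistical analyses says: "Appropriate adjustments for multiple primary (depression and anxiety) tests will be made, i.e. Bonferroni correction". The stated aim is to hold the type I error at 5%.

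The planned size is 38 per group, raised to 48 per arm (96 in total) for 20% attrition. It is attributed to a calculation "using a sample size formula comparing time-averaged differences for continuous outcomes in repeated measurement studies", with d = 0.40, a within-subject correlation of 0.70 and four assessment points.

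**The concern.** Both sections claim the same 5% study-wide error but divide it differently. The power paragraph divides by five. The analysis section names a family of two. The power paragraph also conflicts with itself, since it counts two primary outcomes a few words before dividing by five.

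At stake is how a primary result is read. A p-value of 0.015 on one subscale would miss the level stated in Participants and meet the level implied in Statistical analyses. Patients and investigators are not blinded to allocation, so it is better that no choice of threshold remains open when results are seen. The per-test level is also an input to the sample size, and the sample size cannot be re-derived until one value is fixed.

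**Working it through.** **1. The divisor.** Two outcomes give 2 tests. Two outcomes at three follow-ups would give 6. Neither count is 5, and the article lists no other primary test.

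- Bonferroni over two tests: 0.05/2 = 0.025.
- Two tests at 0.01: study-wide level at most 2 × 0.01 = 0.02.
- Two tests at 0.025: at most 2 × 0.025 = 0.05.
- The stated identity holds only for five tests: 5 × 0.01 = 0.05.

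**2. The plan's own sample size.** Inputs from Participants: d = 0.40 (SD 1), ρ = 0.70, m = 4 assessments, power 0.80, two-sided. The usual formula for a time-averaged difference, assuming equal correlation between all visits, is

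n per group = 2 (z₁₋α/₂ + z₀.₈₀)² × V / d², with V = [1 + (m − 1)ρ]/m = (1 + 3 × 0.70)/4 = 0.775.

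- α = 0.01: 2 × (2.576 + 0.842)² × 0.775/0.16 = 113.1, so 114.
- α = 0.025: 2 × (2.241 + 0.842)² × 0.775/0.16 = 92.1, so 93.

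The stated 38 is not reproduced at either level. This formula returns 38.02 if the factor 2 is left out and α is 0.05 two-sided, which matches neither 0.01 nor 0.025. The attrition step is correct: 38/0.8 = 47.5, so 48 per arm and 96 in total.

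**3. The model in Statistical analyses.** It uses three follow-ups with baseline as covariate. Taking ρ = 0.70 between all visits, V = [1 + 2 × 0.70]/3 − 0.70² = 0.80 − 0.49 = 0.31.

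- α = 0.01: 45.3, so 46 per group.
- α = 0.025: 36.8, so 37 per group.

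**4. Chance that the two levels disagree.** With n = 38 per arm, power is Φ(d/√(2V/n) − z₁₋α/₂), and the chance that p falls between 0.01 and 0.025 is the difference between the two powers.

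| Method | d/√(2V/n) | Power at 0.01 | Power at 0.025 | Difference |
|---|---|---|---|---|
| Time-averaged, m = 4, V = 0.775 | 1.98 | 28% | 40% | about 12% |
| Baseline-adjusted, 3 visits, V = 0.31 | 3.13 | 71% | 81% | about 10% |

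These chances are per subscale and hold if the true effect is d = 0.40. If there is no effect, the chance per subscale is 0.025 − 0.01 = 0.015.

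**The case against.** The strongest reply is that 0.01 appears only among the assumptions of the power calculation, and that Statistical analyses is the sole analysis rule. On that view there is one decision rule, and planning at a stricter level than the analysis uses is merely conservative. Part of this stands: 0.01 is a planning input, and 0.025 is inferred from Bonferroni over two named tests. It does not remove the discrepancy. The power paragraph presents 0.01 as what a study-wide 0.05 means for a single test, and the analysis section claims the same 5% for a family of two. The full protocol may explain the five, but this is a conflict between two printed statements, not a detail left out of the article.

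Three stronger readings are tempting, and the document supports none of them.

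- **That type I error is inflated.** For the two named tests, both levels stay within 5%. A reader might add that testing every visit on both subscales at 0.025 would exceed 5%. The plan does not say it will do that, and its power calculation targets a time-averaged difference.
- **That the choice of level explains the stated sample size.** The described formula gives 38 at neither 0.01 nor 0.025.
- **That moving to 0.025 repairs the design because power becomes 81%.** That figure belongs to the baseline-adjusted model. Under the formula the power paragraph describes, it is 40%.

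**Conclusion.** The point holds as an inconsistency in the per-test level. The division by five is unexplained, does not match the two primary tests named in both sections, and does not yield the stated study-wide 0.05 for two tests. The consequence is ambiguity over p-values between 0.01 and 0.025, with a chance of about 10% to 12% per subscale if d = 0.40 is true. This rests on 38 analysed per arm, ρ = 0.70 between all visits, and a normal approximation. The failure of 38 per group to follow from the described formula is a separate and larger matter. It bears here because correcting the level alone would leave the sample size unsupported by the method described.

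**What to change.** State one rule in both Participants and Statistical analyses: two primary tests, namely the time-averaged treatment effect on HADS depression and on HADS anxiety (the quantity the power formula addresses), each at two-sided 0.025. Remove the division by five. If five tests were intended, list them and use 0.01 in both places. Holm's procedure at 0.05 is an optional alternative to plain Bonferroni.

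Then restate power or required size at the chosen level and name the method. Per arm after 20% attrition:

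| Method | 0.01 | 0.025 |
|---|---|---|
| Time-averaged, four assessments | 114/0.8 = 142.5, so 143 | 93/0.8 = 116.25, so 117 |
| Baseline-adjusted, three follow-ups | 46/0.8 = 57.5, so 58 | 37/0.8 = 46.25, so 47 |

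Only the last cell fits within the planned 48 per arm.

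The wording costs two sentences and one recalculation, and should be settled before outcomes are compared between arms. Any change in recruitment would follow from the recalculation and the method chosen, not from the wording.
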